### Study procedures

2.4

A scheme of procedures along the visits is presented in Figure 1.

#### Cardiopulmonary exercise testing

2.4.1

Maximal functional capacity is evaluated with an incremental and symptom‐limited cardiopulmonary exercise testing (CORTEX Metamax 3B) on a bicycle ergometer, beginning with a workload of 10 W and increasing gradually in a ramp protocol at 10‐W increments every 1 minute. We define maximal functional capacity when the patient stops pedaling because of symptoms, and the respiratory exchange ratio (RER) is ≥1.05. During exercise, patients will be continuously monitored with 12‐lead electrocardiogram and blood pressure measurements every 2 minutes. Gas exchange data and cardiopulmonary variables are averaged every 10 seconds values. PeakVO2 is considered the highest value of VO2 during the last 20 seconds of exercise. The VE/VCO2 slope is determined by measuring the slope across the entire course of exercise.^20^ Each subject will undergo three tests (at baseline, 15 days, and 30 days).

#### Echocardiography

2.4.2

Two‐dimensional Doppler echocardiogram is performed under resting conditions. Each subject will undergo three examinations (at baseline, 15 days, and 30 days). All parameters, including tissue Doppler parameters, are measured according to current guidelines of the European Society of Echocardiography.^21^

#### Cognitive assessment by MMSE and MoCa

2.4.3

MMSE and MoCa tests will be used to assess the cognitive abilities and evaluate the impact of the intervention on cognitive function.^22^ Each subject will undergo three tests (at baseline, 15 days, and 30 days). Overall scores will be analyzed.

#### Health‐related QoL

2.4.4

MLHF questionnaire^23^ will be used to assess the impact of the intervention on QoL. Each subject will undergo three tests (at baseline, 15 days, and 30 days).

#### Continuous ECG recording

2.4.5

The heart rhythm and rate are continuously recorded during 30 days by remote monitoring systems integrated into clothing (Nuubo Suite License).

#### Serum biomarkers

2.4.6

Three blood samples (at baseline, 15 days, and 30 days) are collected under standardized conditions for biomarkers' profiling. Prognostic biomarkers in HF will be analyzed,^24^ NT‐proBNP and CA125 will be measured by electrochemiluminescence immunoassay.

### Sample size calculation

2.5

The null hypothesis of the study is that the mean peakVO2 absolute differences from baseline to 15 days after the withdrawal of beta‐blockers will be similar. The sample size determination for this study assumes two‐sided testing at the 0.05 significance alpha level. Because this is a randomized clinical trial, we assume no differences in peakVO2 at baseline among the two arms. Based on a prior study of our group in HFpEF, we assume eligible patients will have a mean (SD) peakVO2 of 10 ± 2.8 mL/kg/min.^8^ Along the same line, and based on prior studies about the deleterious effects of heart rate slowing in HFpEF patients, we speculate a blocker withdrawal will increase peak VO2 about 10%. With this data in mind, we assume a mean change of 1.2 mL/kg/min and a common SD of 2.0,^8^, ^25^, ^26^ a clinical meaningful change according a recent HFA position paper that consider significant clinical changes of peakVO2 those greater than 6% when baseline peakVO2 is lower than 14 mL/min/1.73 m^2^.^27^

Assuming an allocation ratio of 1:1, a total of 42 patients (21 patients per group) would provide 90% of power at a significance alpha level < 0.05. Assuming 20% of withdrawals or losses to follow‐up, a total of 26 patients per arm (52 patients) will be enrolled. The software used for sample size calculation was “xsampsi” from Stata 14.1.

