### Study design

2.1

This study is designed as a multicenter, prospective, controlled, randomized, two‐arms, cross‐over, efficacy trial. The population includes patients with the diagnosis of stable HFpEF according to criteria of the European Society of Cardiology^18^ and New York Heart Association functional (NYHA) class II‐III/IV. A computer‐generated randomization sequence previously designed will be used to allocate participants (in a 1:1 ratio) to receive: (a) withdrawal of beta‐blocker followed by beta‐blocker reintroduction in two periods of 15 days; or (b) continuation of beta‐blocker followed by beta‐blocker withdrawal in two periods of 15 days. A summary of the study design is described in Figure 1. The study will be conducted in two centers in Spain. Discounting the time due to staggered entry, the total duration of a patient's follow‐up will be 6 months. All patients will provide signed informed consent before randomization. The research ethics committee approves the protocol of our center following the principles of the Declaration of Helsinki and national regulations.

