### Study population sampling

2.2

Candidate patients will be selected from the outpatient HF‐clinics of the Hospital Clínico Universitario of Valencia‐Spain and Hospital Clínico Universitario de Santiago‐Spain. Treatment will be following current guidelines^18^ and HF educational programs of each institution. Briefly, HFpEF is defined as the presence of: (a) symptoms and signs of HF with normal (≥50%) left ventricular ejection fraction (LVEF); (b) elevation of natriuretic peptides; and (c) increase in LV wall thickness and/or increased left atrial (LA) size as a sign of increased filling pressures. Inclusion and exclusion criteria are summarized in Table 1. Inclusion criteria require the presence of ChI after performing the cardiopulmonary exercise testing (CPET). The chronotropic index is equal to (heart rate at peak exercise−resting heart rate)/([220 – age] − resting heart rate).^19^ ChI is defined as a chronotropic index <0.62.

**Table 1 clc23345-tbl-0001:** Inclusion and exclusion criteria

Inclusion criteria	Exclusion criteria
Stable symptomatic heart failure (NYHA functional class ≥II) during the last month.	Inability to perform a valid baseline exercise test
Diagnosis criteria of HFpEF according to ESC guidelines: (a) symptoms and signs of HF (b) left ventricular ejection fraction >50% by Simpson method (c) NT‐proBNP >125 pg/mL in the last month (d) at least one additional criterion: 1. relevant structural heart disease (LVH and/or LAE); and/or 2. diastolic dysfunction	Significant primary pulmonary disease; including pulmonary arterial hypertension, chronic thromboembolic pulmonary disease or chronic obstructive pulmonary disease
	Patient with prior history of left ventricular ejection fraction <50%
	History of an acute coronary syndrome in the previous 12 months
Adults >18 years old	Effort angina or signs of ischemia during CPET
Previous admission for acute heart failure	Significant primary moderate to severe valvular disease
Previous treatment with beta‐blockers during the last 3‐month	Any other comorbidity with a life expectancy lower than 1 year
	Chronic treatment with digitalis or calcium channel blockers
Chronotropic incompetence assessed by CPET, defined as: [(HRmax − HRrest)]/[(220 − age) − (HRrest)] < 0.62	HR at rest >75 bpm
	Uncontrolled blood pressure, defined as systolic blood pressure > 140 mmHg and/or diastolic blood pressure > 90 mmHg.

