#### Treatment intervention and visits

2.3.2

Following screening (visit 0) and randomization (visit 1) visits, the procedures across treatment arms are:

*‐A‐arm*: Patients allocated to this arm are instructed to reduce by half the dose of beta‐blocker (Figure 1). The patients will be advised for potential adverse effects and instructed to contact with outpatient's clinics of HF if any adverse effect occurs. Patients will be checked in 3 days (visit 2) by a cardiologist. If clinically stable, the patients are instructed to withdraw the beta‐blocker and repeat all the procedures of the study at 15 days (visit 3). After visit 3, the patients initiate the previous half dose of beta‐blockers. Patients are visited at 18 days (visit 4). If clinically stable, the patient will increase to the previous dose of the beta‐blocker and repeat all the examination tests at 30 days (visit 5).

*‐B‐arm*: Patients allocated to this arm will continue with the same treatment and revisited 3 days after (visit 2) (Figure 1). All of the study procedures repeated at 15 days (visit 3), and, after them, the patients are instructed to reduce by the half dose of beta‐blocker. Likewise, the patients are advised for potential adverse effects and instructed to contact outpatient HF‐clinics of HF if any adverse effect occurs. Patients are revisited in 3 days (at 18 days, visit 4), and if clinically stable, the patient withdraws the beta‐blocker and repeats all the examination tests at 30 days (visit 5).

At visit 5, the responsible cardiologist will assess all the examination test and individually decide the convenience of beta‐blockers reintroduction or withdrawal in both arms. A cardiologist of the HF‐unit will clinically evaluate all patients at 60‐day after randomization (visit 6). Additional visits will be permitted according to the patient's clinical status and will be registered.

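### The null hypothesis in section 2.5 names no comparator, so it does not define the randomised off-versus-on contrast, and the stated 90% power does not show which test was meant

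*Protocol article*

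**What the plan says.** Section 2.5 (Sample size calculation) begins: "The null hypothesis of the study is that the mean peakVO2 absolute differences from baseline to 15 days after the withdrawal of" beta-blockers; the sentence ends by saying that these differences will be similar. It names one condition, withdrawal, and one change; no second quantity is given.

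Section 2.1 calls the study a "multicenter, prospective, controlled, randomized, two‐arms, cross‐over, efficacy trial". Section 2.3.2 sets out the sequences:

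- Arm A, period 1: after a visit at 3 days, "If clinically stable, the patients are instructed to withdraw the beta‐blocker and repeat all the procedures of the study at 15 days (visit 3"). The drug is then reintroduced, and the tests are repeated at day 30.
- Arm B, period 1: "Patients allocated to this arm will continue with the same treatment and revisited 3 days after (visit 2"). It is tested on drug at day 15.
- Arm B, period 2: the dose is reduced after day 15, then "if clinically stable, the patient withdraws the beta‐blocker and repeats all the examination tests at 30 days (visit 5").

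The primary endpoint in the Introduction is the absolute and relative change in peakVO2 15 days after the intervention, again without a comparator. Section 2.5 assumes a mean change of 1.2 mL/kg/min with a common SD of 2.0, and 21 patients per group (42 in total) for 90% power at two-sided 0.05. Section 2.6 plans a repeated-measures ANOVA between the two intervention groups. Its group-by-time interaction is described as a test of whether time (15 and 30 days) affects the size of the intervention effect.

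**The concern.** The trial asks whether peakVO2 is higher off beta-blocker than on it. A null for that question has to contain both states. This one contains only the off state, which both arms reach: arm A at day 15 and arm B at day 30. A reader cannot tell from it which measurements are to be compared.

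Three things depend on the missing half of the sentence: what the 1.2 and the SD of 2.0 refer to, what power 42 patients give, and which term of the ANOVA is the confirmatory test. If the wrong term is taken as the test of treatment, the analysis could miss a real effect.

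**Working it through.** **1. Which state each measurement represents.** Let the mean on drug at day 15 be m, the effect of being off drug be T, and the day-30 period effect be P. Assume no carry-over.

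| | Day 15 | Day 30 |
|---|---|---|
| Arm A | off: m + T | on: m + P |
| Arm B | on: m | off: m + P + T |

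Section 2.5 assumes equal baselines, so subtracting baseline changes none of the between-arm contrasts below.

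- Day 15, A minus B: (m + T) − m = T. This is a randomised off-versus-on contrast.
- Group means over both visits: A is m + (T + P)/2 and B is m + (P + T)/2. Their difference is 0, so the treatment effect cancels.
- Group-by-time interaction: (A15 − A30) − (B15 − B30) = (T − P) − (−P − T) = 2T. Half of it is T, with the period effect removed. This is the two-period within-patient contrast.

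If group in section 2.6 means randomised arm, the group comparison over days 15 and 30 therefore carries no treatment effect and the interaction carries all of it.

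**2. The plan's own figure.** Inputs, all from section 2.5: difference 1.2, SD 2.0, two-sided 0.05, power 90%. The normal quantiles are 1.960 and 1.282, with sum 3.242 and square 10.507. The figure to reproduce is 42.

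- Parallel day-15 contrast: n per arm = 2 × 2.0² × 10.507 / 1.2² = 58.4, so 59 per arm, 118 in total.
- Paired contrast, 2.0 as the SD of the within-patient difference: N = 2.0² × 10.507 / 1.2² = 29.2, so 30 in total (32 with the t distribution).

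Neither gives 42. A paired contrast needs 42 if the SD of the difference is 1.2 × √42 / 3.242 = 2.40. If 2.0 is instead the SD within each period, the SD of the difference is 2.0 × √(2(1 − ρ)), and 2.40 corresponds to a within-patient correlation ρ of about 0.28. The article gives no correlation. A difference of 1.0 (10% of the assumed mean of 10) with an SD of the difference of 2.0 gives 42.03, but the stated difference is 1.2.

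**3. Power at 42 patients.**

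- Day-15 parallel, 21 per arm: SE = 2.0 × √(2/21) = 0.617; 1.2/0.617 = 1.944; power = Φ(1.944 − 1.960) = 49% (48% with t).
- Paired, SD of the difference 2.0: SE = 2.0/√42 = 0.309; 1.2/0.309 = 3.888; power = Φ(3.888 − 1.960) = 97% (also 97% with t).
- Paired, 2.0 as the per-period SD, ρ assumed: about 77% at ρ = 0, 90% at ρ of about 0.28, 97% at ρ = 0.5.

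**The case against.** The strongest reply is that the intended comparison can be recovered from context. Section 2.3.1 randomises to withdrawal or continuation and calls both interventions. Section 2.5 goes on to assume equal baselines in the two arms, a common SD, 1:1 allocation and 21 per group. Section 2.6 compares two groups. This is two-arm language, and it supports day-15 change in arm A against arm B. It stands as evidence that a randomised comparator was in mind. It does not settle the matter: under that reading power is about 49%, and the crossover design supports the within-patient contrast equally well.

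A second reply is that a journal article condenses the full protocol. That would excuse a missing detail. Here the article does state the null, and the statement is incomplete in a way that the endpoint and the analysis section do not repair.

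A reader might go further and infer that the null can only be a comparison of off with off, which a real effect could never reject, or an uncontrolled test against screening, open to familiarisation or regression to the mean. The document does not support that:

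- Those two readings are not the only ones, as the two-arm wording shows.
- Randomised on-drug data are collected (arm B at day 15, arm A at day 30), and the screening test is itself on drug, because prior beta-blocker treatment is an entry criterion.
- Selection at screening was on heart-rate response ("Inclusion criteria require the presence of ChI after performing the cardiopulmonary exercise testing (CPET")), not on peakVO2. Regression to the mean in peakVO2 is not shown.
- Section 2.6 plans neither an off-versus-off nor a one-sample test, so error rates worked out for those tests are not consequences for this trial.

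**Conclusion.** The point holds as a defect in how the hypothesis is defined. The design and data collection do provide the on-drug comparator. The null in section 2.5 leaves it out, and the article does not say whether the primary test is the day-15 between-arm comparison or the two-period within-patient contrast.

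The stated 90% at 42 patients lies between the two and identifies neither. The parallel figure takes 2.0 as the SD of the change in each arm; the paired figure takes it as the SD of the within-patient difference. The cancellation in the group comparison assumes that group means randomised arm and that there is no carry-over. If group were meant as treatment received, the cancellation would not apply, but the article would still have to say so.

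**What to change.** 1. **Section 2.5, null.** Replace the sentence with, for example: the mean within-patient difference in peakVO2 between the end of the withdrawal period and the end of the beta-blocker period, adjusted for period, is zero.
2. **Section 2.5, sample size.** Say that 1.2 and the SD refer to that difference, say whether 2.0 is the SD of the difference or a per-period SD (and if so, give the correlation assumed), and restate the power for 42 evaluable patients.
3. **Introduction, primary endpoint.** Name the comparator in the same terms.
4. **Section 2.6.** Identify the confirmatory term. With group as randomised arm this is the group-by-time interaction over days 15 and 30, not the group comparison.

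The cost is wording in three places and one recalculation. No visits, tests or patients are added if the within-patient contrast is chosen and its restated power is acceptable. If the sponsor meant the day-15 between-arm comparison instead, that should be stated, and the stated inputs then call for 59 evaluable patients per arm rather than 21. Either way, the choice should be fixed before outcomes are compared.

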**Methods:**

This is a prospective, crossover, randomized (1:1) and multicenter study. After randomization, the clinical and cardiac rhythm will be continuously registered for 30 days. PeakVO2 is assessed by cardiopulmonary exercise testing (CPET) at 15 and 30 days in both groups. Secondary endpoints include quality of life, cognitive, and safety assessment. Patients with stable HFpEF, functional class New York Heart Association (NYHA) II‐III, chronic treatment with beta‐blockers, and ChI will be enrolled. A sample size estimation [alfa: 0.05, power: 90%, a 20% loss rate, and delta change of mean peakVO2: +1.2 mL/kg/min (SD ± 2.0)] of 52 patients is necessary to test our hypothesis.

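### The 1.2 mL/kg/min design effect does not match the expected 10% rise on a mean peakVO2 of 10, and 42 patients at 90% power do not follow from 1.2 with SD 2.0

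*Protocol article*

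**What the plan says.** Section 2.5 (Sample size calculation) of the protocol article builds the calculation in three steps.

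- Baseline: "we assume eligible patients will have a mean (SD) peakVO2 of 10 ± 2.8 mL/kg/min".
- Expected benefit: "we speculate a blocker withdrawal will increase peak VO2 about 10" per cent.
- Design values: "With this data in mind, we assume a mean change of 1.2 mL/kg/min and a common SD of 2.0", with three literature citations attached, followed by a remark that the change exceeds a published 6% threshold for clinical relevance.

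The test is two-sided at 0.05, and the result is that "a total of 42 patients (21 patients per group) would provide 90% of power at a significance alpha level < 0.05". With 20% losses this becomes 26 per arm, 52 in total. The Methods paragraph of the abstract repeats the design values: "delta change of mean peakVO2: +1.2 mL/kg/min (SD ± 2.0".

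Section 2.1 describes a two-arm crossover with two 15-day periods. Section 2.5 names the Stata command used but not the values entered. It does not say whether 2.0 is an SD between patients, an SD of a single measurement or an SD of within-patient differences, and it gives no correlation.

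**The concern.** Two statements in the sample size paragraph do not fit together.

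First, a rise of about 10% on a mean of 10 is 1.0 mL/kg/min. The paragraph moves to 1.2 as if it followed, but 1.2 is 12% of 10. It would be 10% of a mean of 12, which appears nowhere. Required sample size varies with the inverse square of the effect, so the step from 1.0 to 1.2 changes it by a factor of (1.2/1.0)² = 1.44 with all else fixed.

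Second, the sample size does not follow from the inputs given for it. A reader cannot tell which effect the 90% power refers to, or whether the trial is well powered or badly underpowered for the improvement that the authors expect. That matters most if the result is null, when the stated power is what supports reading it as evidence against a worthwhile effect.

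**Working it through.** **Inputs**, all from Section 2.5: two-sided alpha 0.05; power 90%; effect 1.2; SD 2.0; mean peakVO2 10; expected rise about 10%; 42 evaluable patients, 21 per group.

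**Step 1: the effect.** 0.10 × 10 = 1.0 mL/kg/min, and 1.2 / 10 = 12%.

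**Step 2: reproducing the 42.** In the normal formula, (1.96 + 1.2816)² = 10.507. With effect 1.2 and SD 2.0:

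- Parallel groups: n per arm = 2 × 10.507 × 2.0² / 1.2² = 58.4, so 59 per arm (118 in total).
- Crossover, 2.0 as SD of within-patient differences: n = 10.507 × 2.0² / 1.2² = 29.2, so 30 patients.
- Crossover, 2.0 as per-measurement SD with no correlation (variance of differences 2 × 2.0² = 8): n = 10.507 × 8 / 1.2² = 58.4, so 59 patients.

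One-sided versions of the three give 48 per arm, 24 and 48. None gives 42. To reach 42 at an effect of 1.2 one needs an input that the article does not state: a within-patient correlation of about 0.28 with per-measurement SD 2.0 or, for parallel groups, a per-arm SD of about 1.20.

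**Step 3: a combination that does match.** With effect 1.0 and SD of differences 2.0, n = 10.507 × 4 / 1.0² = 42.03. At exactly 42 patients the normal-formula power is 89.98%.

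**Step 4: power of 42 evaluable patients.** Noncentral t, two-sided 0.05, 40 degrees of freedom. The noncentrality is effect / (2.0 × √(2/21)) for parallel groups and effect × √42 / SD of differences for the crossover.

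| Reading of SD 2.0 | Power at 1.2 | Power at 1.0 |
|---|---|---|
| Parallel, 21 vs 21, SD within each arm | 47.5% | 35.2% |
| Crossover, per-measurement SD, correlation 0 (SD of differences 2.83) | 76.5% | 60.9% |
| Crossover, SD of within-patient differences | 96.7% | 88.5% |

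**Step 5: taking 90% at 1.2 as given.** Under noncentral t this forces an SD of differences of about 2.34 (about 2.40 by the normal formula). Power at 1.0 is then 77.1%, and 90% power at 1.0 would need 42 × 1.44 = 60.5, about 61 evaluable patients. This 77% is a different quantity from the 76.5% in the table, which is power at 1.2.

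**The case against.** The article says about 10%, not exactly 10%, and it attaches three citations to the 1.2 and the 2.0. The change may come partly from those sources, and the phrase that links it to the preceding figures is not a stated multiplication. This stands to the extent that a strict arithmetic slip is not proven. It does not remove the conflict: the paragraph presents 1.2 in the light of a mean of 10 and a 10% rise, gives no other reason for it, and the effect used is 20% larger than the effect expected.

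A reader might infer that power falls from 90% to 77% at the expected effect. The documents do not support that as a finding. It takes 90% at 1.2 as true, and that figure does not reproduce. It also needs an SD of differences of 2.34, whereas the only SDs in Section 2.5 are 2.8 and 2.0. The combination in Step 3 uses the stated SD, and under it 42 patients already have close to 90% power at 1.0, so there would be no loss. That combination is itself an inference.

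A reader might also hold that the trial should be powered at 0.6, which is 6% of 10. The 6% threshold is cited only to show that the assumed change is clinically meaningful, and 12% does exceed it. A trial need not be powered at the smallest relevant effect, so this is not an error.

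**Conclusion.** The point holds as an internal inconsistency plus a sample size that cannot be reproduced. The design effect in Section 2.5 and the abstract (1.2, or 12%) conflicts with the expectation stated beside it (about 10%, or 1.0). Separately, 42 evaluable patients at 90% power do not follow from 1.2 and 2.0 under the parallel reading or either crossover reading tried.

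The size of the problem is a range, because the meaning of the SD is not fixed. Power at 1.0 lies between about 35% and 89%, and at 1.2 between about 48% and 97%. These figures assume 42 evaluable patients, two-sided 0.05 and the three readings in the table; a positive correlation would move the per-measurement crossover reading upward. The exact match at an effect of 1.0 suggests that 1.2 may be the misreported number, but the article does not say so. A loss of power is therefore not demonstrated; what is established is that the 90% claim cannot be tied to a stated effect and SD.

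**What to change.** In Section 2.5 and the abstract:

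1. State one design effect: either 1.0 or, if 1.2 is meant, describe it as 12% of the assumed mean and give its own justification.
2. Say whether SD 2.0 is a between-patient, per-measurement or within-patient-difference SD, and give any correlation assumed.
3. Name the formula and the values entered in the software, so that the 42 can be reproduced.
4. Restate the power of the fixed 42 evaluable (52 enrolled) patients for the chosen effect and also at 1.0.

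If 77% at 1.0 is quoted at all, label it as the scenario in which 90% power at 1.2 is taken as given. Power at 0.6 is optional. The cost is a few corrected sentences and figures; no extra patients are needed.

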## INTRODUCTION

1

Heart failure (HF) with preserved ejection fraction (HFpEF) is a heterogeneous syndrome that is the predominant form of HF in western countries.^1^, ^2^, ^3^, ^4^ Chronotropic incompetence (ChI), defined as the inability to increase heart rate during exercise adequately, is commonly present (ranging from 20 to 75%) in HFpEF patients.^5^, ^6^, ^7^, ^8^, ^9^, ^10^, ^11^ Furthermore, ChI has been proposed as a pathophysiologic mechanism associated with poorer outcomes and decreased functional capacity in a subgroup of patients with HFpEF.^8^, ^12^, ^13^

Data from current registries show a high proportion (ranging from 50% to 80%) of beta‐blockers prescription in HFpEF patients regardless of the heart rhythm.^3^, ^14^ Nevertheless, there is no well‐established evidence endorsing the effect of beta‐blockers. For instance, recent studies suggested that patients with an ejection fraction of 50% or greater did not see any benefits from receiving beta‐blockers.^15^, ^16^, ^17^ Even more, the evidence is missing stratifying patients with HFpEF across ChI status.

When ChI is present, beta‐blockers may have negative effects on functional capacity and other surrogates of the disease severity by exacerbating the ChI. Thus, we hypothesize that deprescribing beta‐blockers in this particular scenario will translate into an improvement in short‐term maximal functional capacity. The purpose of this randomized controlled study is to evaluate the short‐term effects of beta‐blockers withdrawal on the functional capacity, cognitive function, and quality of life (QoL) in patients with HFpEF and documented ChI.

The primary endpoint of the study is absolute and relative changes in peak oxygen uptake (peakVO2) at 15‐day after the intervention. The secondary endpoints are: (a) 15‐day absolute changes in cognitive function assessed by the Mini‐Mental State Examination (MMSE) and Montreal Cognitive Assessment (MoCa); (b) 15‐day absolute changes in echocardiogram parameters (E/E' ratio and left atrial volume index); (c) 15 days absolute changes in QoL assessed by Minnesota Living With Heart Failure Questionnaire (MLHF); and (d) 15 days absolute and relative changes in prognostic biomarkers (N‐terminal pro‐B‐type natriuretic peptide ‐NT‐proBNP‐ and serum carbohydrate antigen 125‐CA125‐).

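### The 90% power claimed for 42 patients does not follow from the printed difference of 1.2 and SD of 2.0 without an unstated assumption, and Section 2.5 implies two different values of delta

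*Protocol article*

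**What the plan says.** All inputs are in Section 2.5 (Sample size calculation) of the protocol article.

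- Test: the calculation "assumes two‐sided testing at the 0.05 significance alpha level".
- Baseline: "we assume eligible patients will have a mean (SD) peakVO2 of 10 ± 2.8 mL/kg/min".
- Expected effect in relative terms: "we speculate a blocker withdrawal will increase peak VO2 about 10" per cent.
- Planning values: "we assume a mean change of 1.2 mL/kg/min and a common SD of 2.0".
- Result, with equal allocation to the two arms: "a total of 42 patients (21 patients per group) would provide 90% of power at a significance alpha level < 0.05". This is raised to 26 per arm for 20% losses.

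The abstract repeats the difference of 1.2, the SD of 2.0 and the 90% power, and says that a sample "of 52 patients is necessary to test our hypothesis".

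On the contrast being powered, the Introduction defines the primary endpoint as absolute and relative "changes in peak oxygen uptake (peakVO2) at 15‐day after the intervention". Section 2.1 describes a two-period crossover with 15 days per period. Section 2.6 plans a repeated-measures ANOVA comparing the two groups, with a group-by-time interaction over days 15 and 30.

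**The concern.** The article prints both the inputs and the result of its calculation, so the result should be reproducible. It is not, for two reasons.

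First, an SD of 2.0 could be the SD of change from baseline, the within-patient SD in one period, or the SD of the paired on/off difference. These lead to very different sample sizes, and the text does not choose among them. The phrases about 21 per group and change to 15 days suggest a comparison between arms, while the design is a crossover.

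Second, the relative effect and the absolute effect in the same paragraph do not agree.

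What is at stake is the stated ability of the trial to detect the effect it is designed for. As printed, a reader cannot tell which contrast 42 patients support, or whether the planning power is well above or well below 90%.

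**Working it through.** **Inputs (Section 2.5):** two-sided alpha 0.05 (z = 1.96), power 90% (z = 1.2816), delta 1.2, SD 2.0, 42 analysed. (1.96 + 1.2816)² = 10.51.

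**Step 1: try to reproduce 42 from the printed delta and SD.**

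- Comparison between arms at day 15, with 2.0 as the SD of the outcome compared: n per arm = 2 × 10.51 × (2.0/1.2)² = 58.4. That is 59 per arm or 118 in total (120 by t).
- Crossover, 2.0 as the SD of the within-patient difference: N = 10.51 × (2.0/1.2)² = 29.2. That is 30 in total (32 by t).
- Crossover, 2.0 as the within-patient SD per period: the SD of the difference is √2 × 2.0 = 2.83, so N = 10.51 × (2.83/1.2)² = 58.4. That is 59 in total (61 by t).

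None is 42, and the gaps are larger than the choice between normal and t can explain. One-sided testing at 90% gives 96, 24 and 48 in the same order. The nearest variant is 44, for the third reading at 80% power, which contradicts the stated 90%.

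**Step 2: power with 42 analysed.** The normal approximation is Φ(delta/SE − 1.96), with SE = 2.0 × √(2/21) for the comparison between arms and SD of the difference/√42 for the crossover. The t column uses the noncentral t with 40 degrees of freedom.

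| Contrast and meaning of SD 2.0 | Delta 1.2, normal | Delta 1.2, t | Delta 1.0, normal | Delta 1.0, t |
|---|---|---|---|---|
| Crossover, SD of paired difference | 97.3% | 96.7% | 90.0% | 88.5% |
| Crossover, within-patient SD per period | 78.5% | 76.5% | 63.0% | 60.9% |
| Between arms at day 15, 21 v 21 | 49.4% | 47.5% | 36.7% | 35.3% |

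**Step 3: check delta.** 10% of a mean of 10 is 0.10 × 10 = 1.0 mL/kg/min. The planning value of 1.2 is 12% of that mean.

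**Step 4: a combination of printed figures that gives 42.** Crossover, delta 1.0, SD of the difference 2.0: N = 10.51 × (2.0/1.0)² = 42.03, with power at 42 of 89.98% by normal approximation. By t the same inputs need 45.

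**Step 5: what else would give 42 at delta 1.2.** The SD of the difference would have to be 2.40 (normal) or 2.34 (t). If 2.0 is a per-period SD with correlation ρ between periods, then SD of the difference = 2.0 × √(2(1 − ρ)). Solving gives ρ = 1 − 2.40²/8 = 0.28, or 1 − 2.34²/8 = 0.32. A day-15 comparison adjusted for baseline would need a correlation with baseline of about 0.80. The article states no correlation.

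**The case against.** The strongest reply is that this is a crossover and should be judged as one. Every patient is tested on and off beta-blocker, Section 2.6 uses both time points, and 15 days after withdrawal falls in the second period for the B-arm. On that view, 21 per group is only the 1:1 allocation to sequence. A correlation is an ordinary input to a crossover calculation, one near 0.3 would reconcile 42 with 1.2 and 2.0, and a condensed article may leave it to the full protocol. A rise of about 10% may also be a loose description of 12%.

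Much of this stands, and it rules out two stronger readings.

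- A reader might infer that 42 cannot be obtained under any reading of the design. The documents do not support that: an unstated correlation of 0.28 to 0.32 gives it, and so does delta 1.0 with an SD of the difference of 2.0.
- A reader might infer that the trial has only about 48% power. That figure holds only if the primary test compares the arms at day 15, and Sections 2.1, 2.3.2 and 2.6 describe a crossover with repeated measures.

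Nor would a null result become uninterpretable. It would be read from the estimate and its confidence interval, not from the planned power.

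What remains is that the article does print a delta, an SD, an N and a power, and these four do not fit together without something it does not state. Even on the reading most favourable to the plan, 90% is not the power at delta 1.2; it is about 97%.

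**Conclusion.** The concern holds in this form: the printed delta of 1.2 and SD of 2.0 do not yield 90% power at 42 patients without a further, unstated assumption. At delta 1.2 and 42 analysed, power is about 97%, about 77% or about 48%, depending on the contrast and on what the SD measures. The lowest figure is conditional on a day-15 comparison between arms. These values assume two-sided 0.05, normally distributed outcomes and no correlation beyond what each definition of the SD implies; other correlations would give other values.

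The same paragraph implies delta 1.0 in one sentence and uses 1.2 in the next. That 42 came from a crossover calculation with delta 1.0 and an SD of the difference of 2.0 is an inference from the arithmetic, not something the article says. If it is right, the stated 90% is close to correct (88.5% to 90.0%), and the printed 1.2 does not belong to that calculation.

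**What to change.** In Section 2.5, and correspondingly in the abstract:

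1. Name the within-patient, two-period treatment contrast as the contrast that the sample size supports.
2. State whether delta is 1.0 or 1.2 mL/kg/min, and make the relative effect agree with it.
3. State what the SD of 2.0 refers to, and any correlation used.
4. Restate the power for 42 analysed patients from those inputs. If 2.0 is the SD of the paired difference, that is about 97% at delta 1.2, or about 89 to 90% at delta 1.0.
5. If the primary analysis is to remain a comparison between arms at day 15, state about 48% at delta 1.2.

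The enrolment target of 52 is kept. The cost is a few sentences in two places and possibly a less favourable power figure. Section 3 reports 28 patients enrolled with inclusion still open, so the clarification could be made while recruitment continues.
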